## Background

Accounting for $46-billion - or 36% of public spending on health care [1] - hospitals are a major target for cost reductions through efficiency initiatives in Canada. Some provinces are considering payment reform as a vehicle to achieve this goal. The use of financial incentives to increase hospital efficiency is now widespread in Europe and has occurred in the United States (US) since 1983 [2-4]; however, the approach remains largely untested in Canada [5].

In April 2010, the British Columbia (B.C.) provincial government implemented activity based funding (ABF) for hospitals, marking a fundamental change to the method of funding acute hospital care. ABF will direct up to 20% of available funds to acute hospitals on the basis of types and volume of services. This change is significant in an industry accustomed to historically-based global budgets and unaccustomed to detailed scrutiny of what services are provided to B.C.'s 4.5 million residents and at what cost.

While this change in hospital funding is being implemented in B.C., a debate over the relative merits of hospital ABF is unfolding across Canada [6,7]. For example, the Canadian Medical Association and the B.C. Medical Association have recently staked positions supportive of ABF [8-10], although support for ABF among the medical community is mixed [11,12]. The Canadian Nurses Association supports an increasing emphasis on output measurement [13] but falls short of endorsing ABF, while other groups are calling for more comprehensive baseline data [14]. Although there has been no formal examination of the effects of ABF policies in Canada - in part because B.C. is the first province to adopt ABF for acute hospitals on a large scale - several other provinces are considering adopting similar funding models.

This project will provide an evidence base on the impacts of ABF, including changes in the type, volume, cost, and quality of services provided. Policy- and decision-makers in B.C. and elsewhere in Canada will be able to use this evidence as a basis for policy adaptations and modifications.

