### Data Resources and Variable Construction

The analytic dataset for **Aim 1 **(*internal to the hospital*) will be derived from acute and outpatient DAD hospitalizations linked to the registry data. The dataset will include the following variables: month and year of discharge, CMG, CIHI-defined age group, hospital, region of residence (HA), length of stay (LOS), ICD-10-CA codes, indicator of death, and Adjusted Clinical Groups (a measure of health status [28]). The number of inpatient separations per year, for the conditions to be studied (Table 1), is expected to exceed 5,000. We will analyze hospital separations over the period from fiscal year 2005/2006 through to, and including, 2012/2013, to ensure consistent application of CMG+ across all years.

We will consider the effect of data quality and completeness on the results. The most recent multi-stage randomized studies of DAD data quality, which involve clinical chart re-abstractions, have been conducted by CIHI and have found the majority of data elements in the DAD are accurately reported [35], with comorbidity reporting being an important exception. We will use the results of these studies to exclude those ICD-10-CA codes susceptible to being affected by coding practice changes. Further, we will link Medical Services Plan data to hospital separation data to evaluate completeness of reporting (a means to validate procedure information in the DAD).

One comprehensive analytic dataset will be created for **Aim 2 **(*external to the hospital*) for the years 2005/2006 through 2012/2013. This analytic dataset will be the product of linking acute hospital, registry and continuing care datasets with summarized physician fee-for-service expenditure data. The hospital data will be used to calculate rates of: readmission, admissions from the emergency department and ambulatory care sensitive admissions. The analytic dataset will include admission date, CMG, hospital, region of residence, ICD-10-CA codes, procedure date and whether the patient was admitted from the ED. Readmissions at separate hospitals will be attributed back to the incident hospitalization. The analytic dataset will include an indicator variable to represent incident cases of new home care in the period immediately following discharge from acute care. A variable representing the amount of physician services will be determined from the physician fee-for-service Medical Services Plan (MSP) data linked to patient data.

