### Analysis

Initially, we will provide descriptive analyses of the overall trend in provincial LOS and case mix adjusted volume. We will then construct a multivariate zero-truncated Poisson regression model to identify factors associated with length of stay for each condition included in Table 1. The dependent variable, length of stay of patient *i*, is *Y*_*i*_. The regression model effects include: hospital and patient level effects, ***X***_***i***_, (such as age and ACG). Hospital level clustering will be incorporated into the model. The model is:

where time and policy (and interaction between time and policy) represent study month (1,2,3...) and an indicator variable for ABF, respectively.

If the MoHS changes ABF policy during the study period (e.g., to 30% of acute funding), we will change the parameterization of the model to reflect the change. The parameters of interest are θ and τ, where θ represents an immediate change in the length of stay and τ represents a change in the trend in length of stay. The results will be presented as absolute and relative changes to facilitate interpretation. While we are confident these methods are appropriate for the data and the questions being addressed, if small sample sizes inhibit analysis, we will explore composite measures (which combine multiple conditions) for standardized rates [36-38].

We will use a linear regression model to examine the relationship between ABF and hospitals' case mix adjusted volume of cases (transformed for normality if needed). The dependent variable, *Y*_*i*_, is the hospital's monthly number of case mix adjusted cases. Repeated measures (clustering) on hospitals over time will be incorporated into the model through ***X***_***i***_, a vector of hospital effects. The regression equation is written:

where the parameters of interest are change in level (θ) and change in trend (τ). We will construct a regression model for overall weighted cases plus a separate regression model for each condition included in Table 1.

We will model the number of in-hospital medical and surgical deaths, *Y*_*i*_, (as described in Table 2) relative to the total number of separations, *N*_*i*_, using a Poisson model for count data. The vector ***X***_***i ***_will include hospital effects and adjust for repeated measurements on the same hospital. The regression model is written:

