The parameters of interest are those associated with immediate change in the number of deaths (relative to the number of discharges, *N*_*i*_) and a change in the trend of number of deaths. We will explore the use of zero-inflated Poisson (ZIP) models if we find an abundance of counts of 0.

Similar to the approaches described above, we will use a linear regression model (suitably transformed for normality) to detect changes in hospital expenditures associated with ABF implementation (including adjustments for effects of inflation) and controlling for repeated measures on hospitals.

Following published methods for calculating hospital readmission rates [31], we will calculate overall readmission rates using a multivariate Poisson model for count data, controlling for repeated measures on hospitals. We will also construct separate models for the conditions listed in Table 3. The regression models of monthly hospital readmission rates will include effects for hospital, time and a binary variable for ABF. The parameters of interest represent immediate change in readmission and change in trend over time.

We will use a linear regression model to examine the relationship between the number of (monthly) new home care patients and ABF. The unit of observation will be the number of new home care patients within an HA and we will control for repeated measures over time. The effects of primary interest are those associated with immediate change in new home care patients and a change in the trend of home care patients. Given stable monthly count data at the HA-level, we expect to be powered able to detect moderate and large sized effects.

Similar to the methods described above, we will model the number of monthly readmissions to acute care from home care using a Poisson model for count data and adjust for HA and hospital effects. The parameters of interest are those associated with immediate change in the number of readmissions to acute care from home care and a change in the trend of number of readmissions.

We will also use a log-transformed model to examine the association between patients' fee-for-service physician expenditures (fee-adjusted) over time, and implementation of ABF. The regression equation for patients' fee-for-service, fee-adjusted, physician expenditures is written:

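### The models as described carry no seasonal term, so with an April 2010 start a seasonal outcome biases both the level change θ and the trend change τ

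*Protocol article*

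**What the plan says.** The Analysis section gives the time structure of the length-of-stay model in words: "where time and policy (and interaction between time and policy) represent study month (1,2,3...) and an indicator variable for ABF, respectively". It then defines the targets: "θ represents an immediate change in the length of stay and τ represents a change in the trend in length of stay". The case-mix-adjusted volume model has the same two targets, and its outcome "is the hospital's monthly number of case mix adjusted cases".

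The remaining models (deaths, hospital expenditures, readmissions, new home care patients, readmissions from home care, physician expenditures) are described by analogy or by the same pair of targets. For readmissions the terms are listed: "The regression models of monthly hospital readmission rates will include effects for hospital, time and a binary variable for ABF". That sentence names no interaction, although the text goes on to target a change in trend.

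The other covariates named are as follows:
- Length of stay: "hospital and patient level effects", with age and ACG as examples.
- Deaths: the covariate vector "will include hospital effects and adjust for repeated measurements on the same hospital".
- Elsewhere: health authority, physician and comorbidity effects, and adjustments for inflation and fees.

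Season, calendar month and harmonic terms are not mentioned anywhere in the article. The remark on power for the home care model takes the monthly health-authority counts to be stable.

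On timing, the Background states: "In April 2010, the British Columbia (B.C.) provincial government implemented activity based funding (ABF) for hospitals". Data Resources and Variable Construction states: "We will analyze hospital separations over the period from fiscal year 2005/2006 through to, and including, 2012/2013". The same section lists month and year of discharge among the dataset variables.

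**The concern.** A segmented regression attributes to the policy whatever changes at the break and is not carried by the other terms. A straight line in study month cannot follow an annual cycle. It is natural to think that complete years on each side protect the comparison. They do equalise the average seasonal level, but not the correlation between the cycle and time within a segment. A cycle that is low in the months after April and high in the months before March tilts both fitted lines upwards. The pre-ABF line then ends too high and the post-ABF line starts too low, and the gap appears at April 2010.

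Several planned outcomes could plausibly be seasonal, such as heart failure and chronic lung disease stays, pneumonia deaths and admissions from the emergency department. For an outcome that peaks in December or January, a policy with no effect would look like an immediate fall followed by a rising trend. θ and τ are the results meant for policy-makers. There is no control province (Study Limitations), so nothing in the design removes a shared seasonal pattern. Seasonal variation left in the residual also costs precision.

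**Working it through.** The article gives no seasonal amplitude, power figure or sample-size calculation, so there is no stated figure to reproduce.

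**Inputs from the article.** The time terms are study month, ABF indicator and interaction (Analysis). ABF starts in April 2010 (Background). The data cover fiscal years 2005/2006 to 2012/2013 (Data Resources).

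**Assumptions.**
- Fiscal years run April to March, so month 1 is April 2005, month 61 is April 2010 and month 96 is March 2013 (60 months before, 36 after).
- The interaction is counted from month 61, so that θ is the step at April 2010, as the article defines it.
- There is no true ABF effect and no underlying trend.
- The season is A·cos(2π(m − peak)/12) for calendar month m, where A is half the peak-to-trough range.
- Months have equal weight and the fit is by least squares.

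**Step 1. Seasonal moment per year.** Number the months April to March as k = 1 to 12 and let S = Σ k·s(k) for A = 1. For a January peak, s = 0, −0.5, −0.866, −1, −0.866, −0.5, 0, 0.5, 0.866, 1, 0.866, 0.5. The sum of s is 0 and S = 22.39. A December peak gives the same S, a February peak gives 16.39 and a March peak gives 6.00.

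**Step 2. Slope of each segment.** The slope is (number of years × S) / [n(n² − 1)/12].
- Before: 60 × 3599/12 = 17,995, so 5 × 22.39/17,995 = 0.00622 per month.
- After: 36 × 1295/12 = 3,885, so 3 × 22.39/3,885 = 0.01729 per month.

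**Step 3. Fitted values at month 61.** Each segment mean is 0, so each line passes through 0 at its midpoint.
- Pre-ABF line, midpoint 30.5: 0.00622 × 30.5 = +0.190.
- Post-ABF line, midpoint 78.5: −0.01729 × 17.5 = −0.303.

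**Step 4. Bias.** θ = −0.303 − 0.190 = −0.49A. τ = 0.01729 − 0.00622 = +0.011A per month, or +0.13A per year and +0.40A over 36 months.

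The same steps for other peaks:

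| Peak | Bias in θ | Bias in τ per year |
|---|---|---|
| December or January | −0.49A | +0.13A |
| February | −0.36A | +0.10A |
| March | −0.13A | +0.04A |
| April | +0.13A | −0.04A |
| July | +0.49A | −0.13A |

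For a December or January peak, A = 5%, 10% and 15% give a θ bias of −2.5%, −4.9% and −7.4%. The false trend accumulates to +2.0%, +4.0% and +6.0% over 36 months. The result does not depend on a sine shape: a December-to-February block of +10 points gives θ = −2.3 points and τ = +0.6 points per year.

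**Step 5. With the term added.** Refitting with 11 calendar-month indicators takes both biases to zero. At equal residual variance the standard error of θ is 2.6% wider.

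**Step 6. Effect on tests (illustrative).** This simulation uses a January peak, A = 5% or 10%, no true effect and a nominal level of 5%.
- Single series, residual SD 3% or 5%: θ is falsely significant in 12–15% of runs and τ in 0.1–4%.
- 30 hospitals sharing the cycle, hospital-month SD 10%, hospital-clustered errors: θ is falsely significant in 91% (A = 5%) and 100% (A = 10%) of runs, and τ in 42% and 89%.
- With one annual harmonic added, these rates are about 4–8%.

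**The case against.** **This is a journal article, and its equations are not visible.** The displayed equations could not be read in the text available for this review, and the length-of-stay covariates are given only by example. A reader might infer that every model contains these three time terms and nothing else. The documents do not establish that: the conclusion rests on the prose, and the readmission sentence does not list the interaction. It is more than ordinary condensation, however. The article specifies the time terms, names the target parameters and lists fallbacks (zero-inflated models, transformations, composite measures, re-parameterisation if the policy changes), and season is not among them.

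**Direction and size depend on the outcome.** A reader might infer that seasonality must show as a fall and then a rise. The documents give neither amplitude nor phase for any outcome, and the signs reverse for an April or summer peak. Tables 1 to 3 also include outcomes for which no winter peak is shown, such as joint replacement, appendectomy and carotid endarterectomy. Deaths are modelled relative to separations, and mortality, length of stay and physician expenditure carry patient-level adjustment, so their seasonal amplitude may be smaller than that of raw counts. All of this stands and limits the reach of the point.

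**The trend artefact is the milder one.** Several hypotheses are framed as trend changes, and in a single series false rejection of τ stays below the nominal rate. The high pooled rates depend on an assumed number of hospitals, an assumed SD and a fully shared cycle. This also stands. The bias in the estimates does not depend on those simulations.

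**Working days.** A reader might infer a further bias in monthly totals from the uneven number of working days. Across 16 plausible holiday definitions the bias in θ ran from −0.5% to +1.1%, with no stable sign, so it is not part of this point.

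**Conclusion.** The point holds in conditional form. The models as described give study month, an ABF indicator and, where stated, their interaction as the time terms, with no seasonal term. Under an April-to-March split of 60 and 36 months, any outcome with an annual cycle then yields biased θ and τ even if ABF does nothing. The size is up to about half the seasonal amplitude for θ and 0.13 of it per year for τ. The direction is a false fall and then a rise for December-to-March peaks, and the opposite for April or summer peaks. Outcomes without seasonality are unaffected.

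This rests on the April-to-March fiscal year, a stable annual cycle, θ defined at April 2010, equal monthly weights and the prose account of the models. If a displayed equation or the full protocol already carries a calendar-month term, the point falls for that model.

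**What to change.** State in the Analysis section that each monthly and patient-level model includes calendar-month effects: 11 indicators, or annual Fourier terms where the outcome is sparse. Apply this to length of stay, volume, deaths, readmissions, new home care patients, readmissions from home care, physician expenditures, and hospital expenditures if these are analysed monthly. Write out the readmission model's interaction term, since a change in trend is targeted there.

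No new data are needed, because month of discharge is already in the dataset. The cost is one sentence and about a 2.6% wider standard error of θ at equal residual variance. Where an outcome is seasonal, the smaller residual variance offsets this. An offset for working days or days in the month in the count models is optional.

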#### Information Base for Supporting ABF

The success of ABF is critically linked to the ability to measure 'weighted' hospital output accurately. Methods for characterizing hospital output according to the patients' mix of clinical conditions and interventions have become common and are known as case mix adjustments. The most popular method is diagnosis related groups, or DRGs [20], though variants of DRG have been developed, each customized to address local policy and health delivery characteristics and objectives [21,22]. In Canada, all acute inpatient discharge data submitted to the Canadian Institute for Health Information's (CIHI) Discharge Abstract Database (DAD) are case-mix-adjusted using their Case Mix Group (CMG+) methodology [23]. Case mix adjustment is important since it weights hospital discharges according to their expected relative use of resources (and therefore cost). Each CMG+'s expected relative cost is represented by a resource intensity weight (RIW). As the length of stay has no bearing on the RIW value assigned (with minor exceptions for patients with exceptionally long lengths of stay), the incentive is to shorten lengths of stay in order to keep actual costs below the RIW-based case-specific relative amounts.

The veracity of weighting hospital output by RIW is contingent on accurately reported clinical data. CIHI's clinical chart re-abstractions have shown that Canadian hospitals have modified their clinical coding behaviour to maximize RIWs even in the absence of direct financial incentives to do so [18,19]. This behavior introduces an additional challenge to our study and requires us to be able to differentiate actual changes in activity mix as a result of the changing financial incentives from apparent changes in activity mix that are merely shifts in coding practices.

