### Study Objective

The primary objective of this study is to examine the impact of ABF on acute care hospitals and related services in B.C. This objective will be fulfilled by meeting two specific aims.

**Aim 1**: To measure internal (to the hospital) changes resulting from the shift toward ABF. In a longitudinal analysis of observational data, we will measure whether and how hospitals respond to the changed financial incentives. Related hypotheses include:

**Hypothesis 1.1**: Lengths of stay will decrease and case mix adjusted volume of patients will increase from baseline levels. We will test for changes in trend over time.

**Hypothesis 1.2**: There will be changes in in-hospital quality measures (mortality and adverse events) for specific conditions that are characterized by their variability in clinical utilization patterns. We will test for changes in trend over time.

**Hypothesis 1.3**: Hospitals' expenditures will increase from baseline levels. We will construct a model to detect changes in trend over time of hospital expenditures.

**Aim 2**: To measure external (to the hospital) changes. In a longitudinal analysis of observational data, we will measure whether other components of the health care system are affected by the shift toward ABF. Related hypotheses include:

**Hypothesis 2.1**: There will be an increase in 30 day readmission rate, rate of admissions from emergency department (ED) and rate of admissions for ambulatory sensitive conditions, all indicators of sub-optimal acute care. We will test for an increase in the rates over time.

**Hypothesis 2.2**: There will be an increase in the number of new home care patients subsequent to being discharged from acute care. We will construct a model to detect changes in the trend of: 1) new home care patients over time and 2) readmissions to acute care from home care over time.

**Hypothesis 2.3**: There will be an increase in expenditures on physician services. We will test for an increase in physician expenditures over time.

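### Hypothesis 1.1 concerns volume of patients, but the overall model counts weighted separations, so the readmissions that Hypothesis 2.1 predicts add to volume and can lower mean length of stay

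*Protocol article*

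**What the plan says.** In the Protocol article, Study Objective, Hypothesis 1.1 reads: "Lengths of stay will decrease and case mix adjusted volume of patients will increase from baseline levels". Hypothesis 2.1, in the same section, begins: "There will be an increase in 30 day readmission rate". It treats that rise as a sign of sub-optimal acute care, and Design, Aim 2 describes readmission as a common signal of discharge that came too early.

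The outcomes for Hypothesis 1.1 are built as follows.

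- **Source.** Under Data Resources and Variable Construction, the Aim 1 dataset "will be derived from acute and outpatient DAD hospitalizations linked to the registry data".
- **Unit.** The same section states: "We will analyze hospital separations over the period from fiscal year 2005/2006 through to, and including, 2012/2013".
- **Volume.** In the Analysis section the dependent variable "is the hospital's monthly number of case mix adjusted cases". There is one model for overall weighted cases and one for each Table 1 condition.
- **Weighting.** Information Base for Supporting ABF says of case mix adjustment that "it weights hospital discharges according to their expected relative use of resources". It adds that, apart from exceptionally long stays, the weight does not depend on how long the patient stayed.
- **LOS.** The Analysis section opens with a descriptive provincial trend, then fits a zero-truncated Poisson model for each Table 1 condition.

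The variables listed for Aim 1 contain no admission date, readmission flag or index-stay indicator. The only rule that ties a readmission to its index stay concerns readmissions at a different hospital, and it stands in the description of the Aim 2 dataset. Nothing connects the readmission result to the volume or LOS result.

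**The concern.** Patients and separations differ by the repeat stays. If ABF shortens stays and some of those patients return within 30 days, one episode becomes two weighted cases. The first keeps its full weight although it was shorter, and the second brings a weight of its own. Mean LOS per separation falls whenever the two stays average less than the single stay they replace.

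Both parts of Hypothesis 1.1 then move in the predicted direction because of a change that Hypothesis 2.1 predicts and regards as unfavourable. The Discussion gives the policy objective as greater hospital efficiency without loss of quality, and shorter stays with higher volume would readily be read that way. At stake is whether the volume result can support a statement about patients treated, and whether the two results together can support a statement about efficiency.

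**Working it through.** The plan states no readmission rate, effect size or power figure on this point, so there is no figure to reproduce. The mechanism follows from the definitions above. The sizes below rest on assumed inputs.

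**1. One episode (assumed lengths).** A 10-day stay becomes 5 + 5 days: cases go from 1 to 2, mean LOS from 10 to 5, and days per patient stay at 10. With 6 + 8 days, mean LOS is 7 although days per patient rise to 14. The second stay therefore need not be short.

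**2. All separations together.** Assume that a share s of stays changes from 8 days to 5 days plus a 4-day readmission, and that a readmission weighs as much as its index stay.

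- Volume change = s
- Days per patient = (1 − s)·8 + s·9
- LOS per separation = days per patient / (1 + s)
- LOS of index stays only = (1 − s)·8 + s·5

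| | s = 0.02 | s = 0.05 |
|---|---|---|
| Volume | +2.0% | +5.0% |
| Days per patient | 8.02 (+0.25%) | 8.05 (+0.6%) |
| LOS per separation | 8.02/1.02 = 7.86 (−1.7%) | 8.05/1.05 = 7.67 (−4.2%) |
| LOS, index stays only | 7.94 (−0.75%) | 7.85 (−1.9%) |

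No additional patient is treated and acute days rise slightly, yet volume goes up and LOS per separation goes down. A little under half of the LOS fall (0.75 of 1.7, 1.9 of 4.2) is a real shortening of index stays. The rest comes from counting the second stay separately.

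**3. Starting from a baseline readmission rate.** With index admissions fixed and readmissions per index admission moving from r0 to r1 (assumed), volume changes by (1 + r1)/(1 + r0) − 1. If total bed-days are also fixed, LOS per separation changes by (1 + r0)/(1 + r1) − 1.

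- 8% to 9%: volume +0.9%, LOS −0.9%
- 8% to 10%: 1.10/1.08, volume +1.9%, LOS −1.8%
- 8% to 12%: 1.12/1.08, volume +3.7%, LOS −3.6%

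Counting index cases only, the volume change is 0% in each row.

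**4. Table 1 condition models.** Design, Aim 1 keeps only stays in which the condition is the primary reason for hospitalization. If a share q of readmissions meets that test, the volume change is (1 + q·r1)/(1 + q·r0) − 1. For r0 = 20% and r1 = 25% (assumed):

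- q = 20%: 1.05/1.04, +1.0%
- q = 50%: 1.125/1.10, +2.3%
- q = 100%: 1.25/1.20, +4.2%

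**5. Unequal weights.** If a readmission carries w times the weight of its index stay, the volume change in step 2 becomes w·s. Weights differ by case mix group, and the documents give no value for w.

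**The case against.** The strongest reply is that separations are the right unit for Aim 1. That aim asks how hospitals respond to changed financial incentives, and the payment described under What is Activity Based Funding? flows on the number of cases. Extra paid admissions are part of the response, and dropping them would hide behaviour that the study is meant to detect. This stands, and it is why all weighted cases should not be replaced as the volume outcome. It does not justify reading that outcome as volume of patients.

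The Analysis section does speak of "The dependent variable, length of stay of patient" *i*, which could be taken as days per patient. But LOS is listed as a variable on hospitalization records, separations are what is analysed, and no step sums days over a patient's stays.

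Three stronger readings are tempting and are not supported:

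- **That both stays always enter the LOS regression.** That regression is fitted by Table 1 condition, with the condition as primary reason. A return for a complication or another diagnosis does not enter it.
- **That the apparent effects would be wholly artefact.** Step 2 shows that index stays do shorten in the same example.
- **That the plan books one event as both success and harm.** Hypothesis 1.1 is stated as an expected response, not a success, and it stands beside a predicted rise in hospital expenditures. Readmissions are modelled and reported in their own right, so the harm is not hidden.

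It may also be said that a condensed article leaves episode definitions to a fuller plan. Here, though, the article itself states the outcome and its unit, and that unit differs from the one in the hypothesis.

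**Conclusion.** The point holds in a limited form. The overall weighted-case model can confirm the volume part of Hypothesis 1.1 with no additional patient treated, and the descriptive provincial LOS trend can fall with no acute day saved. Both happen if the readmissions predicted by Hypothesis 2.1 materialize. The condition models are exposed only in so far as readmissions share the primary condition.

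The documents do not give the size. On the assumed inputs, the volume effect is about 1% to 5% in the overall model if weights are equal, and it scales with the relative weight of the readmission. Separate reporting under Aim 2 would show that readmissions rose, but not how much of the Aim 1 result they account for. This is a matter of what Hypothesis 1.1 can conclude. The planned outcomes remain valid as measures of response to per-case payment, and a cheap addition closes the gap.

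**What to change.** Keep all weighted cases and LOS per separation as planned. Beside them report, with the same level (θ) and trend (τ) terms:

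- (a) weighted volume of index cases, excluding 30-day readmissions;
- (b) acute days per patient within a fixed window from index admission, for example 60 days. A 30-day window from admission would miss some readmissions that fall within 30 days of discharge.

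State that shorter stays and higher volume will be interpreted as more patients treated, or as efficiency, only where (a) also rises and (b) also falls.

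The cost is small. The 30-day readmission linkage and the admission date are already planned for the Aim 2 dataset and need only be carried into Aim 1. The downsides are two further outcome series to fit and report, and incomplete follow-up for index admissions in the last weeks of 2012/2013. Classifying stays in the first 30 days of 2005/2006 also needs a short look-back; otherwise those days are left out of (a).
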